## **6.2 Treatment Planning for whole breast irradiation and dose prescription**

Radiotherapy is administered after full recovery from surgical resection, usually after 5 weeks of BCS. Patients will receive computed tomography-based 3-dimensional treatment planning. The total dose to the breast is 40.05 Gy in 15 fractions. The use of intensity-modulated radiotherapy and deep inspiration breath hold techniques is permitted. No tumor bed boost or regional nodal irradiation shall be delivered.

Target contouring of the CTV-breast is performed according to the ESTRO-guidelines. An additional margin for inter- and intrafractional positioning uncertainties of 5-10 mm is added to

generate the PTV-breast. The PTV-breast\_EVAL (generated by subtraction of the 3 mm below the skin from the PTV-breast) should receive 95%-107% of the prescribed dose.

| Organ at risk        | Dose constraints                                                                                         |
|----------------------|----------------------------------------------------------------------------------------------------------|
| Heart                | $D_{\text{mean}} < 3 \text{ Gy}$ , $D_{\text{max}} < 30 \text{ Gy}$ (minor violation $< 40 \text{ Gy}$ ) |
| Ipsilateral Lung     | $D_{\text{mean}} < 8 \text{ Gy}$ , $V_{20\text{Gy}} < 10\%$ (minor violation $< 15\%$ )                  |
| Contralateral Breast | $D_{\text{mean}} < 3 \text{ Gy}$ , $D_{\text{max}} < 20 \text{ Gy}$                                      |
| Spinal cord          | $D_{\text{max}} < 45 \text{ Gy}$                                                                         |

Dose constraints of normal tissue will be respected according to QUANTEC reports (Bentzen et al. 2010; Marks et al. 2010).

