### 6.4 Study visits

After screening of patients for inclusion and exclusion criteria and having received informed consent, appropriate patients will be recruited to the trial. Study relevant data will be collected and patient history will be assessed. Patients will be randomized 1:1 to one of the two study arms. The baseline visit (To) will be scheduled -7 to -1 day before planned treatment start. During the baseline visit (To) a clinical assessment as well as analysis of cosmesis and quality of life including fatigue is planned (and FACIT Fatigue Assessment Questionnaires, see 6.4). Patients will also receive photographic documentation for cosmetic assessment.

Patients in arm A are treated with BCS followed by hypofractionated WBI with a total dose of 40.05 Gy in 2.67 Gy single doses 5 weeks (+/- 2 week) after surgery when wound healing is completed. Patients treated in arm B will receive BCS followed by intermediate single-shot IOERT to the tumor cavity with a dose of 21 Gy prescribed to the 90%-isodose line.

Both groups will be evaluated after BCS at 5 weeks after treatment start (Study Visit 1), to assess to potential influence of IORT on fatigue (secondary endpoint). In group A this time point corresponds to 5 weeks after BCS, just before the start of RT; in group B this corresponds to 5 weeks after BCS incl. IORT.

After the first study visit patients will receive regular follow-up visits based on the standard follow-up program of current German guidelines. The second, third, fourth and fifth study visits are planned 12 weeks (primary endpoint), 6 months, 2 and 5 years (secondary endpoints) after the treatment start. These visits will include a clinical assessment as well as analysis of quality of life including fatigue (EORTC and Fatigue Assessment Questionnaires, BREAST-Q and BCTOS, see below for details). Photographic assessment of cosmetic results is also planned except for the last visit after 5 years. The last subject in (LSI) will be followed 5 years after baseline. This is considered the final study visit.

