#### - Baseline Visit (To)

Baseline Visit will be performed after inclusion of the patient into the study protocol. The baseline visit will be scheduled -7 to -1 day before planned treatment start/BCS.

The following examinations will be performed:

- Clinical assessment using CRF
- Quality of life using the EORTC QLQ-C30, BREAST-Q and BCTOS
- Fatigue assessment using the Fatigue Assessment Questionnaire (FACIT – Fatigue Scale)
- Photographic documentation for cosmetic assessment

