#### - Study Visit (T1)

The first study visit is scheduled 5 weeks (+/- 2 week) after treatment start in both groups. As group B receives irradiation with intraoperative electron radiotherapy, this visit will also take place 5 weeks after RT for group B.

The following examinations will be performed:

- Clinical assessment using CRF
- Quality of life using the EORTC QLQ-C30, BREAST-Q and BCTOS
- Fatigue assessment using the Fatigue Assessment Questionnaire (FACIT – Fatigue Scale)

- Photographic documentation for cosmetic assessment
- Assessment of adverse events

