| Documentation of AEs                              |                                       | X                       | X                        |                          |                         |                         |
| Photographic documentation of cosmetic assessment | X                                     | X                       | X                        |                          | X                       |                         |
| CRF Form                                          | X                                     | X                       | X                        | X                        | X                       | X                       |

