### **9.1 Adverse Events**

Toxicity associated to irradiation that occurs for the first time after treatment start or preexisting toxicity that significantly increases in the severity grade after the start of study treatment likely to be related to radiotherapy will be documented within the subject's medical records and eCRF. Treatment related side effects will be recorded according to CTCAE v5.0 (Common Terminology Criteria for Adverse Events version 5.0; <http://www.eortc.be/services/doc/ctc>). Grades refer to the severity of the adverse event.

Acute toxicities are defined by the occurrence within the first 90 days after the start of RT. Adverse Events occurring after the first 90 days until 6 months after study treatment will be documented as subacute toxicities. Any adverse event emerging more than 6 months after RT will be recorded as late toxicities.

Standardized informed consent forms for irradiation of breast cancers are utilized to inform the patient about study treatment. Expected acute side effects of RT include radiation dermatitis, fatigue, pain, soreness and dryness of the breast, pruritus of the skin, hairloss in the axilla, sore

throat and change in breast size, shape and color. Characteristics and severity of subacute/ late side effects depend on the location and the extent of the target volume/ irradiation field and include skin fibrosis, change in breast size, shape and color, lymphoedema, lung fibrosis, rib fractures, cardiac disorders like cardiac arrhythmia, cardiac insufficiency and coronary heart disease, soft tissue necrosis as well as brachial plexopathy.

Acute/ subacute toxicities will be assessed prior, during and after RT, including:

- Skin disorders: radiation dermatitis, dryness and pruritus of the skin, hairloss in the axilla, lymphedema
- Breast disorders: pain, swelling, change in breast size, shape and color
- Endocrine disorders: hot flashes, night sweats, bone pain
- Lung disorders: coughing, dyspnea
- Gastrointestinal disorders: nausea and vomiting
- Other disorders: alopecia, weight loss

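### Section 9.1 promises toxicity assessment before, during and after RT, but the schedule has no toxicity grading at T0 in either arm and none during or at the end of WBI

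*Protocol*

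**What the plan says.** Section 9.1 makes a general promise for both arms: "Acute/ subacute toxicities will be assessed prior, during and after RT, including". A list of skin, breast, endocrine, lung, gastrointestinal and other disorders follows. The same section counts as toxicity a radiation-related effect that is new after treatment start, or a pre-existing one whose grade rises significantly. Such events go into the medical records and eCRF, graded by CTCAE v5.0. Acute means arising within 90 days of the start of RT.

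Section 6.4 sets the visits. For T0: "The baseline visit will be scheduled -7 to -1 day before planned treatment start/BCS". Its list holds a clinical assessment on the CRF, questionnaires and photographs, but no adverse-event item. For T1: "The first study visit is scheduled 5 weeks (+/- 2 week) after treatment start in both groups". The lists for T1 and for T2 (week 12) both include adverse events. The work-flow row "Documentation of AEs" agrees: it is marked at T1 and T2 and blank at T0. (It is also blank at T3 to T5, although Sections 2.2 and 7.1.2 place toxicity at those visits. That is a separate mismatch.)

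On the position of T1 relative to RT, Section 6.4 says of group A: "In group A this time point corresponds to 5 weeks after BCS, just before the start of RT". Of group B it says: "As group B receives irradiation with intraoperative electron radiotherapy, this visit will also take place 5 weeks after RT for group B".

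Section 10.2.3 compares adverse-event frequencies between arms by chi-squared test, with descriptive p-values.

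**The concern.** The schedule cannot deliver what Section 9.1 promises. In group B the only visit before RT is T0, and no toxicity is graded there. In group A the visit after T1 is T2, so the whole WBI course passes without a scheduled assessment.

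Two things are at stake. First, Section 9.1 counts worsening of pre-existing toxicity, which presupposes a starting grade. Several listed items (pain, hot flashes, night sweats, bone pain, dyspnea) can be present beforehand in women aged 50 or over. Second, acute toxicity is a secondary endpoint compared between arms, and the two scheduled assessments sit at different distances from RT in each arm. Part of any observed difference could then reflect when women were asked rather than what the treatment did.

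**Working it through.** **Inputs.**
- WBI start, Section 6.4: "hypofractionated WBI with a total dose of 40.05 Gy in 2.67 Gy single doses 5 weeks (+/- 2 week) after surgery", so week 5, window 3 to 7.
- Number of fractions, Section 6.2: "The total dose to the breast is 40.05 Gy in 15 fractions". Check: 15 × 2.67 = 40.05 Gy.
- T2, Section 6.4: week 12, window 10 to 14.
- Course length: fractions per week are not stated. I assume five, so 15 / 5 = 3 weeks. Section 1.1 gives 3 to 5 weeks for standard courses of this kind.

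**The protocol's own interval.** The T2 paragraph puts T2 in group A seven weeks after WBI. Counted from the start of WBI this reproduces: 12 − 5 = 7. Counted from the end it does not: 12 − (5 + 3) = 4. With T2 at week 12, seven weeks after the end of a 3-week course would need a start at week 12 − 7 − 3 = 2, outside the 3-to-7 window.

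**Gap from the end of WBI to T2.**
- Nominal, 3-week course: 12 − 5 − 3 = 4 weeks.
- Nominal, 5-week course: 12 − 5 − 5 = 2 weeks.
- 3-week course, shortest within windows: 10 − (7 + 3) = 0 weeks.
- 3-week course, longest within windows: 14 − (3 + 3) = 8 weeks.

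**Scheduled adverse-event assessments relative to RT (nominal).**

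| | Before RT | During or at end of RT | After RT |
|---|---|---|---|
| Group A (WBI) | T1, just before WBI but 5 weeks after surgery | none | T2, about 4 weeks after the end |
| Group B (IORT) | none | no practical meaning for a single dose | T1 at 5 weeks, T2 at 12 weeks |

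T0 contributes nothing in either row. Group A's T1 comes after surgery, so it is not a pre-treatment grade either.

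**Share of the 90-day acute period elapsed at T2.** Group A: 7 × 7 = 49 days from the start of RT. Group B: 12 × 7 = 84 days. The acute period is therefore followed to different depths even if both visits are kept exactly.

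**The case against.** The strongest reply is that Section 9.1 does not rely on visits alone. A reaction that arises in the last week of WBI and clears before T2 is still recordable, because toxicity is documented when it occurs and acute toxicity is defined by occurrence, not by presence at a visit. This stands. A reader might infer that acute WBI toxicity is measured only about four weeks after WBI, or that earlier reactions go unrecorded; the documents do not support that. Nor do they support an estimate of the share of reactions lost. They give no rate at which reactions settle, and such an estimate would count only what is still present at T2.

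Baseline is not empty either. Section 5.6 has relevant illnesses at consent documented. T0 has a clinical assessment, medical history, medication and the QLQ-C30, which covers pain, dyspnea and nausea/vomiting. A blank adverse-event cell before treatment is also normal in itself. All of this stands, but it does not close the gap. Event-driven recording begins after treatment start, so it cannot supply the assessment before RT. As described in Section 7.1.2, the QLQ-C30 does not cover hot flashes or night sweats, and it yields no CTCAE grade.

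A reader might also infer that the schedule works against APBI. That is not shown. IORT reactions that settle before week 5 can be missed in the same way. The missing T0 grade is common to both arms. Group A attends for 15 fractions, which gives more occasions for unscheduled recording.

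Finally, the comparison is descriptive and no confirmatory claim rests on it. That limits the consequence but does not remove the contradiction.

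**Conclusion.** The contradiction holds. Section 9.1 cannot be met by the schedule in Section 6.4: no toxicity grading is scheduled before treatment in either arm, and none during or at the end of WBI. In group A the nominal gap from the end of WBI to the next scheduled assessment is about 4 weeks. That figure assumes five fractions a week; it is 2 weeks for a 5-week course, and about 0 to 8 weeks within the visit windows for a 3-week course.

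The consequence is a lack of systematic grading comparable between arms for acute toxicity, a secondary endpoint analysed descriptively. The direction and size of any bias cannot be determined from the protocol. The primary endpoint is unaffected, since the FACIT Fatigue Scale is listed at T0 and at T2.

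**What to change.** 1. Reconcile Section 9.1 with the T0, T1 and T2 lists and the work-flow table, and state whether the seven weeks in the T2 paragraph run from the start or the end of WBI.
2. Add CTCAE grading of the Section 9.1 items at T0 in both arms, as baseline status rather than as adverse events.
3. At T1 and T2 in both arms, record the worst grade since the previous assessment. T2 then covers the WBI period in group A.
4. Compare worst acute grade between arms relative to the T0 grade. State alongside it that T2 falls about 49 days after the start of RT in group A and 84 in group B, because these changes do not remove that difference.

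If a form at the end of WBI is also used, treat it as supportive. It would exist in one arm only and would add unequal ascertainment.

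The cost is edits to the table, visit lists and CRF, and a few minutes at visits that already take place. The drawback is some recall error in worst-grade recording, notably at T2, which looks back over about seven weeks (12 − 5). Treatment is unchanged.

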## **9.2 Serious Adverse Events**

A serious adverse event is an adverse event with a special degree of severity in that it

- leads to death (CTCAE grade 5)
- is life-threatening (CTCAE grade 4) due to its actual and documented severity at the point of occurrence (not only life-threatening in principle if occurrence was more severe)
- causes or prolongs hospitalization
- is a congenital anomaly/ birth defect
- leads to a lasting or otherwise significant impairment
- is an otherwise significant medical incident

The following examples are not to be considered SAE:

- Medical or surgical interventions
- Hospital admissions that are not the consequence of a medical condition (e. g. social/ convenience admissions)
- day-to-day fluctuations of pre-existing illness(es) or toxicity present or detected at the start of the study that do not worsen
- A planned hospitalization where admission did not take longer than anticipated
- Tumor progression and all medical intervention performed to offer respective therapy or relieve the symptoms of such progression

## 10. Statistical Considerations

### 10.1 Sample Size Calculation

The sample size calculation is based on the primary endpoint change of fatigue from baseline to week 12 after Treatment start (study visit T2 ) between the groups APBI and WBI measured via the FACT-Fatigue score. An improvement in 6 of 13 items by one point is considered clinically relevant resulting in a clinically relevant effect size of 6 points. Assuming a standard deviation of 12 and with a type I error rate of  $\alpha = 0.05$  (two-sided), a two sample t-test requires a total sample size of n=172 patients (86 per group) to achieve a power of  $1 - \beta = 0.90$  for revealing an effect of 6 points. Adjusting for the covariates baseline fatigue, age, and tumor size in a linear model is assumed to yield less unexplained variance and thus to an additionally increased power. Taking a dropout rate of 15% percent into account, n=202 patients need to be randomized. Sample size calculation was carried out using ADDPLAN v 6.1.

### 10.2 Analysis

#### 10.2.1 Analysis sets

The full analysis set (FAS) includes all randomized patients and they will be analyzed according to the treatment they were randomized to.

The per-protocol population (PP) is a subset of the FAS set and comprises all patients, who were treated according to the randomized treatment as outlined in the protocol without major protocol violations.

The safety population will consist of all patients who received one of the study treatments at least once, and patients will be allocated to the treatment they actually received. This will be the primary analysis set for the safety analysis.

Each patient's allocation to the different analysis will be defined prior to the analysis. The allocation will be documented in the statistical analysis plan. During the data review, deviations from the protocol will be assessed as „minor” or „major”. Major deviations from the protocol will lead to the exclusion of a patient from the PP analysis set.

#### 10.2.2 Confirmatory analysis

The null hypothesis to be tested states that the change in the FACT-F score between baseline and week 12 after treatment start is equal for both groups:

$$H_0 : \mu_{APBI} = \mu_{WBI}$$

This hypothesis will be tested at a two-sided level of significance of  $\alpha = 0.05$  against the alternative hypothesis:

$$H_1 : \mu_{APBI} \neq \mu_{WBI}$$

The hypothesis test will be conducted using a linear model with the dependent variable “change in FACT-F score between baseline and week 12 after treatment start” and the independent factors treatment group (A/B), baseline FACT-F score, tumor size, and age. The effect estimate for the treatment group will be calculated alongside a 95% confidence interval.

The confirmatory analysis will be primarily based on the FAS which is consistent with the intention-to-treat (ITT) principle by including all patients who were randomized to the two groups.

Missing data for the primary outcome variable will be replaced using multiple imputation taking the covariates treatment group, baseline FACT-F score, tumor size, and age into account by application of the fully conditional specification method. This will be realized using the option “FCS” of the SAS “MI” procedure which is implemented in SAS 9.4. M=10 imputations will be done and the regression approach will be used to impute the data.

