#### Fatigue

Fatigue will be assessed additionally at time points 5 weeks, 6 months, 2 years, 5 years after treatment start.

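### The imputation model repeats the primary model's covariates, so the planned multiple imputation only returns the adjusted complete-case estimate; the week-5 FACIT score should be added as an auxiliary variable

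*Protocol*

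**What the plan says.** Protocol section 10.2.2 states that "Missing data for the primary outcome variable will be replaced using multiple imputation", "taking the covariates treatment group, baseline FACT-F score, tumor size, and age into account by application of the fully conditional specification method". It adds that "M=10 imputations will be done and the regression approach will be used to impute the data". The confirmatory linear model in the same section has the "independent factors treatment group (A/B), baseline FACT-F score, tumor size, and age". The two lists are the same.

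FACIT is measured at other visits as well. Section 7.1.2 says "Fatigue will be assessed additionally at time points 5 weeks, 6 months, 2 years, 5 years after treatment start", and section 6.4 says "The first study visit is scheduled 5 weeks (+/- 2 week) after treatment start in both groups", which is before the week-12 endpoint visit (T2). Section 6.4 also places this week-5 visit (T1) just before radiotherapy starts in group A, and after the intraoperative dose in group B. Neither the T1 score nor the 6-month (T3) score is among the imputation variables.

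Section 10.1 provides for missing outcomes: "Taking a dropout rate of 15% percent into account, n=202 patients need to be randomized". The sensitivity analysis named in section 10.2.3 is the per-protocol analysis.

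**The concern.** Multiple imputation helps the primary estimate when the imputation model knows something that the analysis model does not. Here it knows nothing more. A woman without a T2 score is imputed as average for her arm, baseline score, tumour size and age, whatever she reported at week 5.

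Section 10.2.2 presents the full analysis set as consistent with intention to treat because all randomized patients are included. Under the stated method, those without a T2 score are included in form but add no information on the treatment effect. If loss to follow-up is related to fatigue after baseline, and differently in the two arms, the planned analysis cannot correct for it, although a relevant score is already collected. The treatment burden between T1 and T2 does differ: group A starts 15 fractions at about week 5, while group B has finished its radiotherapy.

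**Working it through.** **1. The plan's own figure.** Inputs from section 10.1: effect 6, SD 12, two-sided alpha 0.05, power 0.90. The noncentral t gives power 0.8999 with 85 per arm and 0.9032 with 86, so 86 per arm and 172 in total, as stated. 172 / 0.85 = 202.4, which the plan takes as 202. Expected missing: 0.15 × 202 = 30.3 women.

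**2. Why the imputation adds nothing.** Let o and m index women with and without a T2 score, X the shared design matrix and b the complete-case least-squares estimate, so that Xo'yo = Xo'Xo b. Imputed outcomes have mean Xm b. The expected estimate from a completed data set is (X'X)^-1 (Xo'Xo b + Xm'Xm b) = b. This needs complete covariates; it needs no assumption about correlations or dropout.

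**3. The noise from M=10.** With about 15% missing, the between-imputation variance is roughly 0.15 times the squared SE. At SE 1.60, the SD of the difference from complete case is about √(0.15 × 1.60² / 10) = 0.196 points, and about 0.062 with M=100.

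**4. Simulation, setting 1.** N=202, 1:1, true effect 6, about 15% missing, four-covariate model, 1,500 trials per scenario. Assumed, not in the protocol: score SD 12 at each visit, one common between-visit correlation (0.5 or 0.7), the dropout models, and T1 and T3 observed in everyone. Entries are bias in points (Monte Carlo error 0.03 to 0.04).

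| Dropout (correlation) | Complete case | Planned MI | MI + T1 | MI + T1 + T3 |
|---|---|---|---|---|
| Completely random (0.5) | -0.015 | -0.008 | -0.022 | -0.011 |
| Completely random (0.7) | +0.021 | +0.014 | +0.032 | +0.027 |
| T1-driven, both arms alike (0.5) | -0.026 | -0.028 | -0.025 | -0.005 |
| T1-driven, both arms alike (0.7) | +0.040 | +0.040 | +0.048 | +0.058 |
| T1-driven, WBI arm only (0.5) | -0.649 | -0.652 | -0.017 | -0.026 |
| T1-driven, WBI arm only (0.7) | -0.536 | -0.534 | -0.009 | -0.002 |
| T2-driven, WBI arm only (0.5) | -1.874 | -1.881 | -1.673 | -1.570 |
| T2-driven, WBI arm only (0.7) | -1.313 | -1.320 | -1.098 | -1.015 |

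Planned MI and complete case differ on average by at most 0.008 points. Their per-trial difference has SD 0.17 to 0.21 with M=10 and 0.05 to 0.07 with M=100, in line with step 3. Average SE (completely random, correlation 0.5) is 1.62 for planned MI and 1.60 for complete case.

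**5. Simulation, setting 2.** 101 per arm, 2,500 trials, SD 12, correlation with baseline 0.5 and T1–T2 correlation 0.7. With T1-driven dropout in the WBI arm only (logit slope 1.2 per SD), planned MI gives 5.16, a bias of -0.84. Adding T1 and T1 × arm gives 6.02, with SE 1.56 against 1.58. With T1–T2 correlation 0.8 the bias is -1.05 and is again removed.

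The bias is larger here than in setting 1 because T1 says more about T2 beyond baseline. The T1–T2 covariance left after baseline, in SD² units, is 0.7 - 0.5² = 0.45 and 0.8 - 0.5² = 0.55, against 0.5 - 0.5² = 0.25 and 0.7 - 0.7² = 0.21 in setting 1.

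**6. Where T1 helps less.** With setting-2 inputs but WBI-arm dropout driven by an unobserved week-8 score, bias is -0.81 as planned, -0.31 with T1 and -0.18 with T1 and T3. If half of the dropouts also lack T1 (and T3 is unavailable), T1-driven dropout leaves -0.39 of -0.84. Week-8-driven dropout then leaves -0.62 of -0.89 with T1, or -0.55 with T1 and T3.

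**The case against.** The planned method is a conventional missing-at-random analysis, and section 10.2.2 contains no contradiction or arithmetic error. Dropout explained by arm, baseline fatigue, tumour size or age is already handled by the model. The protocol gives no data on why women would drop out. Section 5.5.4 lists terminations that arise at or soon after surgery, such as intraoperative re-classification and incomplete resection. These are not caused by fatigue and may precede T1, although section 5.5.2 asks for continued follow-up as far as possible. The simulated T1-driven biases are all below one SE (1.05 against 1.58), and every biased scenario understates the APBI benefit, so none points to a false claim of superiority. All of this stands, and it limits the size of the point.

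It does not touch the equivalence in step 2. Nor is this a detail left to the SAP: the protocol itself fixes the variables, the method, the SAS option and M.

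A reader might infer that the plan keeps any bias from fatigue-related dropout. That goes too far: there was no material bias when T1 drove dropout equally in both arms. A reader might also infer that adding T1 and T3 cures the problem. That holds only where dropout follows the T1 score and T1 is observed. In group A, T1 precedes WBI, so it cannot record exhaustion during WBI.

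**Conclusion.** The point holds in a limited form. With complete covariates, the planned imputation equals the adjusted complete-case analysis apart from about 0.2 points of simulation noise per trial. This follows from the stated variable lists alone.

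The size of any bias is conditional. If week-5 fatigue drives dropout in the WBI arm only, it is about -0.5 to -1.05 points, or 9% to 18% of the 6-point effect (0.53/6 and 1.05/6), against the trial's own hypothesis. If dropout follows the unseen week-12 score in that arm, it is -1.3 to -1.9 points, and adding T1 and T3 recovers only about 0.3 of that. These figures rest on assumed correlations and dropout models. The protocol does not show that arm-specific, fatigue-related dropout will occur, so it does not support saying that the primary estimate is biased. It supports saying that the imputation, as specified, offers no protection if such dropout occurs.

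**What to change.** Leave the confirmatory linear model unchanged. In section 10.2.2, add the T1 FACIT score as an auxiliary variable in the FCS imputation, either separately by arm or with a T1 × arm term, because T1 is before WBI in group A and after IORT in group B. Raise M above 10; M=100 cuts the noise to 0.05 to 0.07 points.

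T3 may be added to the primary imputation if the analysis can wait about three months. Sections 4 and 6.4 place the last primary-endpoint visit in April 2021 and T3 at 6 months rather than 12 weeks. Otherwise use T3 in a sensitivity analysis. Add a delta-adjusted (missing-not-at-random) sensitivity analysis, since T1 cannot carry fatigue that arises during WBI and some dropouts will lack T1.

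Cost: no new data or patients, and no loss of precision in the simulations (SE 1.56 against 1.58 in setting 2). The imputation model becomes somewhat more complex, with auxiliaries that are themselves incomplete and about 101 women per arm, and the primary analysis comes later if T3 is used.

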### 6.3 Randomization

After initiation of the study, patients will consecutively be screened and eligible patients will be enrolled into the study. To achieve comparable intervention groups, patients will be allocated in a concealed fashion in a 1:1 ratio by means of randomisation using a centralised web-based tool ([www.randomizer.at](http://www.randomizer.at)). Randomization will be stratified with respect to invasive tumor size ( $\leq 1 \text{ cm}^3$ ,  $> 1 \text{ cm}^3$ ) and age ( $\leq 60$  years,  $> 60$  years). Block randomisation with varying block lengths will be performed to achieve in total equal group sizes.

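### Minor, cost-free improvement: with M=10 imputations fixed for the only confirmatory test, a borderline verdict can turn on the random-number stream

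*Protocol*

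**What the plan says.** Section 10.2.2 defines one confirmatory comparison, the change in fatigue score from baseline to week 12. "This hypothesis will be tested at a two-sided level of significance of" 0.05, in a linear model with treatment group, baseline score, tumor size and age, primarily on the full analysis set of all randomized patients. Missing values of the primary outcome are imputed by fully conditional specification in SAS, "taking the covariates treatment group, baseline FACT-F score, tumor size, and age into account". The number of imputations is then set: "M=10 imputations will be done and the regression approach will be used to impute the data".

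Section 10.1 gives the expected loss of patients: "Taking a dropout rate of 15% percent into account, n=202 patients need to be randomized". That is about 0.15 × 202 = 30 women. The protocol gives no separate rate for a missing week-12 questionnaire.

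**The concern.** Multiple imputation fills the gaps with random draws, so the pooled estimate and its p-value depend partly on the random-number stream. The noise shrinks as M grows and is usually ignored when M is large. Here M is small, imputation is expected to feed the primary p-value for a visible share of patients, and one p-value decides the trial. If the result lands near 0.05, whether it counts as significant is partly a matter of chance in the software. The protocol itself fixes M, so this is not a detail left to the statistical analysis plan.

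**Working it through.** **Inputs.** Effect: "resulting in a clinically relevant effect size of 6 points". "Assuming a standard deviation of 12". Two-sided alpha 0.05, 1:1 allocation, 202 randomized, 15% dropout and M=10, all from sections 6.3, 10.1 and 10.2.2. Two assumptions are added. The 15% is read as the share of missing week-12 outcomes, missing at random. The share of outcome variance explained by the covariates, which the protocol does not give, is set at 0% or 25%.

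**The plan's own figure.** The protocol states that "a two sample t-test requires a total sample size of n=172 patients (86 per group) to achieve a power of" 0.90. The t-test calculation gives 85.03 per group, rounded up to 86 (172 in total), with power 0.903. Then 172/0.85 = 202.35, against 202 stated. The sample size is reproduced to within one patient.

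**Monte Carlo noise.** The pooled estimate has Monte Carlo variance B/M, where B is the between-imputation variance. The imputation model uses the same covariates as the analysis model, so B as a share of the total variance is close to the missing share, 0.15 (simulated fraction of missing information 0.153 to 0.156). Hence noise/SE = sqrt(0.15/M):

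| M | Formula | Simulated |
|---|---|---|
| 10 | sqrt(0.015) = 0.122 | 0.12 |
| 50 | sqrt(0.003) = 0.055 | 0.056 |
| 100 | sqrt(0.0015) = 0.039 | 0.039 |

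With 86 completers per group and no covariate gain, SE = 12 × sqrt(2/86) = 1.83 points, so the noise at M=10 is 0.122 × 1.83 = 0.22 points. For other missing shares at M=10, 5% gives sqrt(0.05/10) = 0.07 SE, 10% gives 0.10 SE and 25% gives 0.16 SE.

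**Effect on a borderline p-value.** Two Monte Carlo SDs around z = 1.96 give 1.96 ± 0.245, that is z from 1.715 to 2.205 and p from about 0.086 to 0.027. The simulation held each dataset fixed and re-imputed it with new random draws, using regression imputation, Rubin's rules and small-sample degrees of freedom. The pooled standard error then varies too, and the central 95% of runs is wider at the upper end:

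| Many-imputation p | Range with M=10 | Wrong side of 0.05, M=10 | Wrong side, M=100 |
|---|---|---|---|
| 0.04 | about 0.02 to 0.08 | 29% to 30% | 2% |
| 0.05 | about 0.027 to 0.098 | at the threshold | at the threshold |
| 0.06 | about 0.03 to 0.11 | 25% | 3% to 5% |

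With M=100 the range for p = 0.05 narrows to about 0.041 to 0.061.

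**How often it matters.** The chance that two runs disagree is approximately the density of z at 1.96 times the mean absolute difference between two noise terms, which is 1.128 × noise.

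- Covariates explain 0%: expected z = 6/1.83 = 3.28, which is 1.32 above 1.96, with normal density 0.167 there. M=10: 0.167 × 1.128 × 0.122 = 2.3%. M=100: 0.167 × 1.128 × 0.039 = 0.7%.
- Covariates explain 25%: SE = 1.83 × sqrt(0.75) = 1.585 and z = 3.79, which is 1.83 above 1.96, with density 0.075. M=10: 1.0%. M=100: 0.3%.

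Repeated simulations at the 6-point effect gave 1.2% to 4.1% with M=10 and 0.3% to 1.1% with M=100.

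**Validity and efficiency.** With M=10 the simulated type I error is 0.049, and power at 6 points is 0.89 to 0.97 depending on the covariates, with no clear difference from M=100. Relative efficiency against unlimited imputations is 1/(1 + 0.15/10) = 98.5%.

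**The case against.** The strongest reply is that nothing here is wrong. M=10 is a valid choice, the method is well specified, type I error and planned power hold, and any finite M leaves some dependence on the random draws. At the planned effect the p-value would usually be far from 0.05. The 15% is a dropout allowance and not a forecast of missing week-12 scores. All of this stands, and it is why the point is minor.

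A reader might go further in three ways that the documents do not support.

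- **That M=10 costs power.** Relative efficiency is 98.5%, and the simulations show no clear power difference from M=100.
- **That analysts are free to choose the answer because no seed is given.** A seed is ordinary content of a statistical analysis plan, which section 10.2.1 foresees and which is not at hand, so its absence from the protocol is no finding. A pre-set seed would make the result reproducible. It would not make a borderline result less arbitrary, so the argument for a larger M does not depend on it.
- **That imputing the change score throws away observed week-12 scores from women without a baseline score.** Section 6.4 does say the baseline visit is outside clinical routine in group A. But the same section schedules the fatigue questionnaire at baseline for every patient, and the protocol gives no rate of missed baseline visits. Any size put on this would rest on invented rates.

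**Conclusion.** The point holds as a minor, free improvement and not as an error that threatens the trial. With M=10 and 15% of outcomes missing, the treatment estimate carries noise of about 0.12 standard errors, and the significance verdict can turn on the random-number stream when the p-value falls near 0.05. At the planned 6-point effect this affects about 1% to 4% of trials, against about 1% or less with M=100. The figures assume outcomes missing at random at the dropout rate and covariates explaining 0% to 25% of the variance. With 25% missing (assumed), the simulated disagreement at 6 points rises to about 3% to 6.5% with M=10. The validity of the test is not in question.

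**What to change.** In section 10.2.2, replace M=10 by at least M=100. Nothing else in the imputation model or the confirmatory analysis needs to change. The cost is one number in the protocol and minutes of computing time, with no additional patients or data. The change should be made before the outcome data are analyzed.
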